#### Multiparametric MRI (mpMRI)

MRI will be acquired and reported in accordance with PI-RADS v2.1 and national guideline standards. Scanning will be performed using 1.5 T or 3 T MRI systems (< 10 years old) equipped with multi-phased array surface coils. Only scanners meeting PI-QUAL v2 score 2–3 will be approved. The mpMRI protocol includes T1w, T2w, DWI, and DCE sequences. Butylscopolamine may be administered to optimize image quality. MRI studies below predefined quality thresholds must be repeated. Each center will submit sample imaging for approval prior to patient enrollment, undergo pre-monitoring by the PRIMA core team, and receive annual on-site monitoring. All radiology departments are Q2-certified according to German Radiological Society criteria.

#### Prostate biopsy

MRI/US fusion targeted biopsies (TB) and systematic 12-core biopsies (SB) will be performed via transrectal or transperineal access under local or general anesthesia. TB consists of 4 targeted cores per lesion (up to 3 lesions). Participating urologists must demonstrate certification and ≥ 100 lifetime fusion biopsies, following a standardized QA protocol. Implementation adherence will be monitored as detailed in the quality handbook.

#### MR in-bore biopsy

For participants with PI-RADS 4–5 lesions and negative TB or TB + SB, MR in-bore biopsy will be offered after consensus reading. Needle placement will be confirmed in two imaging planes, and 2–4 cores per lesion will be acquired, with additional cores permitted if targeting is inaccurate.

#### Randomization scheme

Men with PI-RADS 4–5 or PI-RADS 3 with PSAD > 0.15 will be randomized 1:1 into Arm A (TB only) or Arm B (TB + SB).

### Criteria for discontinuing or modifying allocated interventions {11b}

Because PRIMA is a diagnostic accuracy trial without therapeutic intervention, no modification or dose adjustment of assigned study procedures is possible. However, allocated biopsy procedures may be discontinued or deferred for an individual participant under the following circumstances:Participant decision or withdrawal of consent at any point prior to or during the biopsy procedure, without a requirement to provide justification and without any impact on subsequent clinical care.Medical judgment of the responsible study physician, if performing the biopsy would expose the participant to unacceptable clinical risk (e.g., acute infection, severe bleeding disorder, anticoagulation that cannot be safely paused, or significant deterioration in health status).Safety considerations arising during the procedure, including uncontrolled pain, vasovagal reaction, or procedure-related complications.Protocol deviations mandated by emergency clinical indications, if continuation is deemed inappropriate for patient safety.

Participants who discontinue or do not complete their allocated intervention will be encouraged to remain in the study for follow-up assessments where possible, and data already collected may be included in analyses according to the predefined statistical plan (intention-to-treat principle).

### Strategies to improve adherence to interventions {11c}

As PRIMA is a diagnostic accuracy trial without therapeutic intervention, adherence is expected to be high. All participants (Arms A and B) benefit from access to high-quality mpMRI and standardized biopsy procedures at experienced centers, which is commonly perceived as advantageous care. All participants receive structured follow-up imaging and, if indicated, MR in-bore biopsy to ensure that csPCa is not missed in either study arm, reducing concerns about randomization.

Adherence will be supported through clear communication, appointment reminders, and direct contact with study nurses. Completion of scheduled procedures will be monitored through the electronic trial database, and adherence metrics will be reviewed in monthly Trial Steering Committee meetings.

### Relevant concomitant care permitted or prohibited during the trial {11d}

All standard medical care for benign prostate conditions and comorbidities is permitted during the trial. Concomitant medications, including anticoagulants or antiplatelet agents, may be continued according to institutional biopsy safety protocols and national guidelines; temporary adjustment for biopsy procedures is allowed according to routine clinical standards.

External mpMRI examinations or prostate biopsies are not prohibited. However, they are strongly discouraged during trial participation because the study protocol provides comprehensive, high-quality diagnostic assessment—including structured imaging follow-up and MR in-bore biopsy where indicated—designed to minimize risk of missed csPCa. If external diagnostic procedures are nevertheless performed due to urgent clinical need or patient request, they must be documented in the trial database and the participant may be withdrawn if protocol integrity is compromised.

### Provisions for post-trial care {30}

All participants are covered by a clinical trial insurance policy arranged prior to the start of recruitment, which provides compensation for any harm directly related to trial participation, including biopsy-associated complications. Standard clinical follow-up and treatment of any medical conditions identified during the trial will continue within routine healthcare services. No additional post-trial interventions are planned, as PRIMA is a diagnostic trial without therapeutic assignment, and all participants receive guideline-based clinical care independent of study completion.

### Outcomes {12}

#### Co-primary outcomes

Detection of clinically significant prostate cancer (csPCa; ISUP ≥ 2)

Defined as the presence of csPCa on histopathology at initial biopsy (measure: histopathological assessment; metric: binary yes/no). Results will be expressed as the proportion of participants with csPCa in each study arm (method of aggregation: proportion), assessed at index biopsy (timepoint).Detection of clinically insignificant prostate cancer (ISUP 1)

Defined as the presence of ISUP grade group 1 cancer on histopathology at initial biopsy (measure: histopathological assessment; metric: binary yes/no). Results will be expressed as the proportion of participants with ISUP 1 cancer in each study arm, assessed at index biopsy.

#### Secondary outcomes

Patient-reported outcomes (EPIC-26, EORTC-QLQ-C30, VAS)

Measured using validated questionnaires (metric: continuous scores), analyzed as mean changes over time and between groups (aggregation: mean differences), assessed at baseline, 30 days, and 12 months.Biopsy-related complications

Defined as adverse events within 30 days post-biopsy (measure: clinical assessment; metric: categorical/binary), summarized as proportions by study arm, assessed at 30 days post-procedure.Biopsy avoidance due to mpMRI triage

Defined as the proportion of participants not undergoing biopsy due to non-suspicious mpMRI findings (PI-RADS 1–2 or PI-RADS 3 with PSAD ≤ 0.15), reported as proportion, assessed at screening.Diagnostic performance of DRE

Defined as the association between DRE findings and biopsy outcomes (metric: sensitivity, specificity), analyzed cross-sectionally at baseline and biopsy.Biopsy approach (transrectal vs. transperineal)

Compared in terms of pain (VAS score) and infection rates (binary), summarized as mean differences and proportions, assessed within 30 days post-biopsy.MR in-bore biopsy yield

Defined as detection of csPCa in participants undergoing MR in-bore biopsy after negative or ISUP 1 results (metric: binary), reported as proportion, assessed within 3 months post-biopsy.Detection of higher-grade cancer (ISUP ≥ 3)

Defined as presence of ISUP ≥ 3 cancer on histopathology (metric: binary), reported as proportion, assessed at index biopsy.Comparison of bpMRI vs mpMRI

Retrospective comparison of detection performance (metric: paired binary outcomes), analyzed using constrained maximum likelihood methods, assessed at baseline imaging.Change in PI-RADS score

Defined as change in PI-RADS category between baseline and follow-up MRI (metric: ordinal change), reported as proportions of up- or downgrading, assessed at 12 months.Index-lesion-only analysis

Detection of csPCa based on index lesion targeting only (metric: binary), reported as proportion, assessed at index biopsy.AI and radiomics validation

Diagnostic performance of AI-based models (metric: AUC, sensitivity, specificity), analyzed retrospectively, assessed using baseline imaging and biopsy outcomes.

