## Introduction

### Background and rationale {6a}

In the German healthcare context, optimizing diagnostic efficiency is essential due to increasing demand for prostate cancer screening and limited reimbursement for mpMRI. Although MRI-targeted pathways have demonstrated clinical effectiveness, evidence for their cost-effectiveness and scalability in Germany remains limited. PRIMA addresses this gap by evaluating a high-quality, quality-assured MRI pathway that could reduce unnecessary biopsies and downstream treatment costs while maintaining diagnostic accuracy. Prostate cancer (PCa) is the most common solid cancer among men in Germany, with around 75,000 new diagnoses and 15,000 deaths annually, representing 25% of new male malignancies [1]. Classical diagnostic algorithms combining PSA, DRE, and 12-core SB lead to both overdetection of indolent PCa and missed csPCa [2]. Overdiagnosis results in unnecessary treatment, side effects, and psychological burden, whereas underdetection may delay curative therapy. Several prospective studies have demonstrated that TB alone provides similar detection proportions of csPCa compared with SB, while significantly lowering detection of clinically insignificant cancers [3–7]. Nonetheless, other reports suggest that SB still adds incremental diagnostic value [8–13]. The absolute additional yield of SB for csPCa detection has been estimated at 4–5% in two randomized trials and a Cochrane review [8–10], while TB alone may reduce the detection of ISUP grade group 1 cancers by up to 40% [7]. More recent data from the PROBASE trial in younger men (45–55 years) in a screening setting demonstrated that SB identified 26% additional csPCa compared with TB alone, whereas TB contributed only 6% additional csPCa [14]. Screening trials such as STHLM3-MRI [11] and Göteborg-2 [12] provided population-level insights. In STHLM3-MRI, MRI-based pathways reduced unnecessary biopsies and detection of low-grade cancers but would have missed ~1.7 csPCa cases for each avoided ISUP 1 diagnosis [11]. Göteborg-2 demonstrated comparable csPCa detection between TB-only and combined strategies, with fewer insignificant cancers in the TB-only arm (0.6% vs 1.2%), though some intermediate-risk cancers were detected only by SB [12]. Together, these studies highlight that MRI-targeted pathways can safely reduce overtreatment but may risk missing a small proportion of csPCa. Within Germany, mpMRI before biopsy is guideline-recommended [15]. However, the routine addition of SB remains under debate. The PROBASE trial, focusing on younger men (45–55 years), revealed that SB detected 26% additional csPCa compared to TB, suggesting that MRI interpretation and tumor biology may differ with age [16]. Furthermore, the PRIME trial recently demonstrated that bpMRI could suffice in older men (median age 65) [17], whereas PRIMA intentionally uses mpMRI to address potential diagnostic challenges in younger and intermediate-risk groups [18, 19]. Beyond diagnostic accuracy, PRIMA integrates patient-reported outcomes (PROs) to assess procedural burden (VAS) and quality of life (EORTC-QLQ-C30, EPIC-26). These outcomes are essential as biopsy techniques evolve from transrectal to transperineal approaches, potentially reducing infection risk and improving patient experience [13]. Quality assurance (QA) is a major element of PRIMA: all radiology centers are Q2-certified, ensuring compliance with PI-RADS v2.1 [20] and PI-QUAL v2 [21] standards, while urologists must document proficiency in ≥ 100 fusion biopsies. Despite robust international data, most trials have mixed cohorts with prior biopsy history, different MRI protocols, or lacked uniform QA. PRIMA is unique in enrolling exclusively biopsy-naïve men with well-defined MRI risk thresholds (PI-RADS 4/5 or PI-RADS 3 with PSAD > 0.15) and applying a standardized national QA framework. The study therefore aims to generate definitive evidence for or against omission of SB in MRI-positive men within a German healthcare setting.

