#### Secondary objectives

To evaluate whether TB alone reduces overdetection of clinically insignificant PCa (ISUP 1) compared with TB + SB.To compare patient-reported outcomes (EPIC‑26, EORTC‑QLQ‑C30, VAS) between arms.To assess complication rates, biopsy avoidance due to mpMRI triage, biopsy approach (transrectal vs transperineal), MR in-bore biopsy yield, ISUP ≥ 3 cancers, stability of PI-RADS on follow-up MRI, and bpMRI vs mpMRI performance.To validate AI and radiomics models for PCa detection.

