## Statistical methods

### Statistical methods for primary and secondary outcomes {20a}

The primary analysis will compare the detection proportion of clinically significant prostate cancer (csPCa; ISUP ≥ 2) between Arm A (TB only) and Arm B (TB + SB) using a non-inferiority framework. Non-inferiority for csPCa detection will be assessed based on the absolute difference in detection proportions (π_TB − π_TB + SB), evaluated using the likelihood score test by Gart and Nam for binomial parameters at a one-sided α level of 0.05. The non-inferiority margin is δ = 13%. Superiority testing for the secondary co-primary endpoint (detection of clinically insignificant PCa, ISUP 1) will be evaluated based on the ratio of detection proportions (π_TB/π_TB + SB) using a one-sided α level of 0.05. All hypothesis tests apply a fixed global significance level of *α* = 0.05.

Secondary outcomes—including biopsy-related complications, biopsy avoidance, diagnostic performance measures, and biopsy approach comparisons—are defined in the Outcomes section according to domain, measurement, metric, method of aggregation, and timepoint. Biopsy-related complications will be summarized as proportions by study arm at 30 days post-procedure. Biopsy avoidance will be reported as the proportion of participants not undergoing biopsy following mpMRI triage at screening. Diagnostic performance outcomes (e.g., DRE, bpMRI vs mpMRI) will be evaluated using standard accuracy measures (e.g., sensitivity, specificity) where applicable.

All detection outcomes are defined as proportions (number of participants with the outcome divided by the number of participants undergoing biopsy in the respective arm). Secondary outcomes will be analyzed descriptively and, where appropriate, using inferential statistical methods.

Patient-reported outcomes (EPIC-26, EORTC-QLQ-C30, VAS) will be analyzed using mixed models for repeated measures (MMRM), including treatment arm, timepoint, and baseline values as covariates.

A detailed statistical analysis plan (SAP) will be finalized and archived prior to database lock and prior to any unblinded analyses.

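### VAS is the stated measure of procedural burden, but no time stated for its between-arm comparison is at or shortly after the biopsy

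*Protocol article*

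**What the plan says.** The Background and rationale (6a) divides the patient-reported instruments by purpose: "PRIMA integrates patient-reported outcomes (PROs) to assess procedural burden (VAS) and quality of life", with EORTC-QLQ-C30 and EPIC-26 as the quality-of-life instruments. The Secondary objectives then list a comparison of all three, ending with "VAS) between arms".

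The Secondary outcomes section (12) treats the three instruments as one outcome, "analyzed as mean changes over time and between groups (aggregation: mean differences"), with the times "assessed at baseline, 30 days, and 12 months". Section 20a applies one repeated-measures model to all three, "including treatment arm, timepoint, and baseline values as covariates".

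Further down the Secondary outcomes list, VAS appears again under biopsy approach (transrectal versus transperineal): "Compared in terms of pain (VAS score) and infection rates (binary), summarized as mean differences and proportions, assessed within 30 days post-biopsy". No day within that window is named.

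**The concern.** The score meant to describe the biopsy itself has been given the timetable of the quality-of-life questionnaires. A pre-biopsy baseline contains no procedural burden, and the next stated time is 30 days later. Change from baseline is a natural summary for EPIC-26 and QLQ-C30. It fits poorly with a score whose purpose is to capture the procedure.

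The contrast between arms is largest at the procedure. The Prostate biopsy section specifies 4 targeted cores per lesion for up to 3 lesions, and the systematic biopsy adds 12. That is 4 to 12 cores in Arm A against 16 to 24 in Arm B. If TB alone is less burdensome, the difference should be easiest to see at or just after the biopsy. A null result at 30 days or 12 months could be reported as no reduction in burden when it reflects only when the question was asked. The Discussion relies on the patient-reported outcomes for its assessment of diagnostic burden, so such a result would carry weight.

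**Working it through.** The plan gives no figure for VAS, so there is none to reproduce. The check is mainly a comparison of sections, followed by two short calculations.

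**1. Purpose against timing.**
- Background (6a): VAS measures procedural burden.
- Secondary objectives (7): VAS is compared between arms.
- Secondary outcomes (12), patient-reported outcomes: baseline, 30 days and 12 months, as mean change.
- Secondary outcomes (12), biopsy approach: pain VAS at some point in the 30 days after biopsy, for access route rather than arm.
- Statistical methods (20a): repeated-measures model with baseline as covariate.

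The arm comparison therefore has three stated times, none of them peri-procedural. The same section gives VAS two timing rules.

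**2. Which text governs.** Section 20a refers to the Outcomes section for the definition of secondary outcomes and includes the timepoint among the items defined there. That section ties several other outcomes to the index biopsy, for example ISUP ≥ 3 detection, but not VAS. The caption of Fig. 1 mentions PROMs only alongside the 12-month follow-up.

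**3. Who contributes at 12 months.** Section 18b has men diagnosed with csPCa leave the trial. The Sample size section expects 50% csPCa with TB + SB and assumes a true difference of −5 percentage points, which gives 45% with TB alone. Before any other loss, the men remaining are at most:
- Arm A: 477 × (1 − 0.45) = 262
- Arm B: 477 × (1 − 0.50) = 239

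The 12-month VAS thus describes men selected by their biopsy result, at rates that the plan expects to differ between arms.

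**4. What a score at the procedure could detect.** For two equal arms, the detectable difference is (1.96 + 0.84) × SD × √(2/n), at 80% power and two-sided 0.05. With n = 477 from the Sample size section, √(2/477) = 0.0648. The documents give no SD for VAS, so SD on a 0-10 scale is an assumption, shown over a range:
- SD 1.5: 2.80 × 1.5 × 0.0648 = 0.27
- SD 2: 2.80 × 2 × 0.0648 = 0.36
- SD 3: 2.80 × 3 × 0.0648 = 0.54

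These figures show what a well-timed score would offer. They do not measure what is lost at 30 days, because the documents contain nothing from which the arm difference at that time could be estimated. They apply to the arm comparison only, since the split between access routes is not given.

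**The case against.** A reader might infer that biopsy pain has gone by day 30, that VAS will then be near zero in both arms, and that the comparison cannot measure procedural burden at all. The documents do not support this. They give no time course for pain, no wording of the VAS item and no recall period. A day-30 item could ask about pain during the biopsy, and the 30-day survey in section 22 actively asks about persistent pain, so the protocol does not treat pain at that visit as absent.

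The biopsy-approach entry also counts against the strong reading. A window of 30 days includes the biopsy day, so a pain VAS may be collected early and could be tabulated by arm as well. It would be wrong to assert that the approach comparison certainly has the same weakness. In addition, the participant timeline refers to a figure that is not shown, and section 43-type detail such as form content is left to the operations handbook, as is usual for an article.

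These points limit the claim but do not remove it. An early VAS in the figure or handbook would conflict with the written outcome definition, and the two would need reconciling. The approach entry does not set a time for the arm comparison. A recalled-pain item would have no meaningful pre-biopsy baseline, yet the stated analysis is change with baseline adjustment. The objection that later VAS values may capture lasting burden is also fair, and they need not be dropped.

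**Conclusion.** The point stands in a limited form. As written, the between-arm comparison of the procedural-burden measure has no assessment at or shortly after the biopsy, and its timing differs from the second VAS entry in the same section. The definition given is poorly matched to its purpose, so this is more than a detail left to another document. A null difference at 30 days or 12 months would be ambiguous between equal burden and late measurement, and the 12-month value is further weakened by the exit of men with csPCa.

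The size of the loss cannot be stated from the documents. A score directly after the procedure would detect about 0.36 points, or 0.27 to 0.54 over the assumed SD range, if all 477 per arm provide it. The conclusion assumes that the Outcomes section governs the timing, as section 20a indicates, and that the VAS item is not a recalled-pain question. The matter concerns one instrument within a secondary outcome. The co-primary endpoints, the sample size and the non-inferiority conclusion are not touched. It should be corrected, but it does not threaten the trial's main result.

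**What to change.** In the Secondary outcomes section:
- Add a VAS recorded at the biopsy visit directly after the procedure, and state the item and its recall period.
- Use that score as the procedural-burden outcome for both the arm comparison and the access-route comparison, as a mean difference adjusted for centre, without change from baseline. Access route is not randomised, so that second comparison remains observational.
- Reconcile the two VAS entries so that one timing rule applies.
- Keep the later VAS only as a supplementary measure of persisting burden.

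In section 20a, keep the repeated-measures model for EPIC-26 and EORTC-QLQ-C30, and describe the VAS analysis separately.

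The cost is one single-item score and one eCRF field at a visit that already takes place, plus the wording changes. The Trial status section describes version 1.0 with nobody enrolled at manuscript submission, so an early change is cheap. Pain that is not scored at the time of the biopsy cannot be scored contemporaneously afterwards.

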### Participant timeline {13}

The participant timeline includes screening, enrollment, baseline assessments, randomization, biopsy procedures, and structured follow-up over 12 months. Only men with mpMRI findings of PI-RADS 4–5 or PI-RADS 3 with PSA density > 0.15 proceed to randomization. Follow-up includes standardized complication reporting, patient-reported outcome assessments, and repeat MRI depending on biopsy results (see Fig. 1).

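### DRE and AI accuracy are defined against biopsy, but only mpMRI-positive men are biopsied; the target population is unstated and partial verification is not addressed

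*Protocol article*

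**What the plan says.** Under Secondary outcomes, the article defines three diagnostic-performance endpoints.

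- **DRE:** "Defined as the association between DRE findings and biopsy outcomes (metric: sensitivity, specificity", analysed cross-sectionally at baseline and biopsy.
- **AI and radiomics:** "Diagnostic performance of AI-based models (metric: AUC, sensitivity, specificity), analyzed retrospectively, assessed using baseline imaging and biopsy outcomes".
- **bpMRI versus mpMRI:** "Retrospective comparison of detection performance (metric: paired binary outcomes), analyzed using constrained maximum likelihood methods". No sensitivity or specificity is named here.

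Statistical methods {20a} then adds: "Diagnostic performance outcomes (e.g., DRE, bpMRI vs mpMRI) will be evaluated using standard accuracy measures (e.g., sensitivity, specificity) where applicable".

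Who is biopsied is fixed elsewhere. Participant timeline {13} restricts randomization: "Only men with mpMRI findings of PI-RADS 4–5 or PI-RADS 3 with PSA density" above 0.15 proceed. The biopsy-avoidance outcome counts the remaining men as "not undergoing biopsy due to non-suspicious mpMRI findings". Sample size {14} puts the mpMRI-positive share at 60%. The article states no reference standard for the unbiopsied men in these endpoints, no correction for partial verification, and no restriction of the DRE and AI endpoints to mpMRI-positive men.

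**The concern.** Whether a man has a reference result depends entirely on the mpMRI-based rule. Sensitivity and specificity computed in the biopsied men are therefore conditional on a positive mpMRI. That is a legitimate quantity, but it is not the accuracy of DRE or of an AI model among men who present with raised PSA or an abnormal DRE. The gap matters most for AI: image-based models are likely to agree with mpMRI, so the men they would correctly call negative are largely those who are never biopsied.

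A second issue is that the reference is not the same in the two arms. Arm A has targeted cores only, so csPCa outside the targets is scored as absent.

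AI validation and bpMRI versus mpMRI performance are both listed under Secondary objectives, and the Discussion presents the AI work as a platform for future diagnostics. A reader who takes the reported figures as population accuracy would be misled on named objectives.

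**Working it through.** **Inputs from the article (Sample size {14}):** mpMRI-positive share 60%; csPCa 50% in the TB + SB arm; true difference −5%; margin 13%; one-sided α 0.05; 477 per arm; 1590 analyzable. I read the 50% as prevalence among mpMRI-positive men, since it is used as the TB + SB detection proportion.

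**1. The plan's own figures.** With the variance under H0 taken at the constrained maximum-likelihood values (0.5405 and 0.4105), s0 = √(0.5405×0.4595 + 0.4105×0.5895) = 0.7003. Under the alternative, s1 = √(0.50×0.50 + 0.45×0.55) = 0.7053. Then n = [(1.645×0.7003 + 0.842×0.7053)/(0.13 − 0.05)]² ≈ 476.02, rounded up to 477. The total is 2×477/0.6 = 1590. Both figures reproduce.

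**2. Verified and unverified men.** Biopsied: 2×477 = 954. Not biopsied: 1590×0.4 = 636.

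**3. AI specificity.** Assumptions not in the article: 7% csPCa in unbiopsied men; a model negative in 80% of MRI-negative men without csPCa and in 30% of MRI-positive men without csPCa.

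- MRI-negative without csPCa: 0.4×0.93 = 0.372 of all men.
- MRI-positive without csPCa: 0.6×0.5 = 0.300.
- All men without csPCa: 0.672.

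True specificity = (0.372×0.8 + 0.300×c)/0.672, where c is the value computed in biopsied men.

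| Computed in biopsied men (c) | True in all enrolled men |
|---|---|
| 20% | 0.3576/0.672 = 53% |
| 30% | 0.3876/0.672 = 58% |
| 40% | 0.4176/0.672 = 62% |

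A binormal simulation gives the same direction. It assumes an AI score as accurate as mpMRI, within-group correlation 0.3–0.8, a cut-off calling 60% of men positive, and csPCa of 5–15% in unbiopsied men. From all men to biopsied men, specificity falls from 0.53–0.56 to 0.22–0.45, AUC falls from 0.77–0.88 to 0.70–0.85, and sensitivity rises from 0.83–0.94 to 0.86–0.97.

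**4. DRE.** If DRE is independent of mpMRI given disease status, there is no bias. For dependence, take 10% csPCa in unbiopsied men: 63.6 with and 572.4 without csPCa. Assume DRE is positive in 40% of MRI-positive and 15% of MRI-negative men with csPCa, and in 20% and 10% of those without.

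- Sensitivity in all men: (0.40×477 + 0.15×63.6)/540.6 = 0.371, against 0.40 computed.
- Specificity in all men: 1 − (0.20×477 + 0.10×572.4)/1049.4 = 0.855, against 0.80 computed.

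Over the dependent scenarios tried (csPCa 5–15% in unbiopsied men, weaker and stronger dependence), sensitivity is overstated by about 1–4 points and specificity understated by about 3–6.

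**5. bpMRI versus mpMRI.** Every verified man is mpMRI-positive under the study rule, so absolute mpMRI figures in that set could only be 477/477 = 100% sensitivity and 0/477 = 0% specificity. In a ratio of true-positive (or false-positive) fractions the denominators cancel, so relative measures survive, provided no bpMRI-positive men sit among the unbiopsied. Illustration: take a verified relative false-positive fraction of 0.90, and suppose 90% of any bpMRI-positive unbiopsied men have no csPCa.

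- 2% of the 636 bpMRI-positive: (429.3 + 0.02×636×0.9)/477 = 0.924.
- 5% bpMRI-positive: (429.3 + 0.05×636×0.9)/477 = 0.960.

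**6. Reference by arm.** With a 5% absolute increment from systematic cores, 477×0.05 ≈ 24 Arm A men with csPCa are scored disease-free. Arm A has 477×0.55 ≈ 262 csPCa-negative results, so about 9% of them (24/262) would be wrong.

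**The case against.** **The natural reading is accuracy among biopsied men.** Only they have biopsy outcomes, and the article nowhere claims accuracy in all enrolled men. This stands in part: a reader might infer that a false population claim is being made, and the text does not make one. But the target is left unstated, and unlabelled sensitivity and specificity invite that reading.

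**The bpMRI endpoint is already a paired comparison.** This stands. Sensitivity and specificity enter only through {20a}, as examples and where applicable. A reader might also infer from the 100%/0% arithmetic that such figures will be reported for mpMRI. No stand-alone mpMRI accuracy is planned, so that arithmetic only shows why absolute metrics should not be used.

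**DRE bias is small.** This stands, and it may be zero.

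**Sensitivity and specificity need not be dropped.** This stands. Among biopsied men they are identified just as AUC is; a population label suffices for DRE and AI.

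**The arm difference is small.** Some 24 men are 2.5% of 954, and relying on Arm B halves the data. The scale is fair, but within Arm A's negatives the share is about 9%. Keeping pooled results as supportive answers the loss of data.

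**Verification bias is detail for the SAP.** The correction method can be left there. The metric and its reference are already fixed in the published outcome definition, so a SAP that keeps them without a population label inherits the problem. Nor does follow-up imaging resolve it, because these endpoints are defined against biopsy and the DRE analysis is cross-sectional.

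**Conclusion.** The point holds for DRE and AI as an unstated target population combined with unaddressed partial verification: 636 of 1590 men have no reference result, by design. The consequence is potentially large for AI specificity (30% computed against about 58% true in the worked case) and modest or nil for DRE. These sizes rest on assumed csPCa rates in unbiopsied men and assumed dependence on mpMRI, none of which the article gives. The direction for AI needs only that the model calls more men negative when mpMRI is negative.

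For bpMRI versus mpMRI the point is narrower: the paired comparison is usable for relative measures, and only the absolute metrics permitted by {20a} would be uninformative. The unequal reference between arms adds about 24 misclassified men on the plan's own increment.

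A reader might infer that the trial's main result is compromised. It is not: the csPCa and ISUP 1 comparisons are between randomized arms of mpMRI-positive men, and neither they nor the sample size depend on the unbiopsied group.

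**What to change.** In Secondary outcomes and in Statistical methods {20a}:

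1. State that DRE and AI accuracy (sensitivity, specificity and AUC) applies to mpMRI-positive biopsied men.
2. For bpMRI versus mpMRI, replace absolute sensitivity and specificity with relative true- and false-positive fractions. Note that these hold only if bpMRI-positive, mpMRI-negative men are absent or are dealt with explicitly.
3. Report DRE and AI accuracy in Arm B (TB + SB) as the main reference set, with both arms pooled as supportive.
4. Report accuracy in the whole enrolled population only as a verification-bias-corrected sensitivity analysis, with the assumptions for unbiopsied men stated and varied.

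The cost is wording plus a small additional analysis. The accuracy claims become narrower, and the main reference set is about half the biopsied sample (477 of 954). The article reports no enrolment at manuscript submission, so the definitions can be clarified well before any data are analysed.
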